### Randomization and allocation concealment

A two-level stratified block randomization scheme will be employed to ensure balance across key demographic variables, given the characteristics of the screened population. The randomization sequence will be generated by a researcher independent of the core study team using the blockrand module (version 1.5) in R software (version 4.4.3). This individual will not participate in any study procedures.

The stratification process will include the following: first-level (stratification) dyads will be stratified into four groups based on two factors: sex (male/female) and age (above/below 71 years). Second level (block size): within each stratum, a block size of 2 is used to ensure an automatic 1:1 allocation ratio between the intervention and control groups.

The allocation sequence will be concealed, and the assignment will be executed in two phases: first, after the initial 52 dyads are completely identified and screened, and second, again for the remaining 50 dyads. This approach ensures that all participants maintain the same probability of assignment and helps maintain balance throughout the recruitment process. This entire procedure will be performed by personnel external to the core research team.

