### Statistical methods

Continuous data will be described using means and standard deviations (SDs) or medians and interquartile ranges (IQRs), depending on their distribution as assessed by the Shapiro–Wilk test. These data will be compared between the intervention and control groups via Student’s *t*-test or the Mann–Whitney *U* test, respectively. Categorical data will be summarized using absolute and relative frequencies and compared between groups via the *χ*^2^ test or Fisher’s exact test, as appropriate.

Outcomes will be analyzed across the baseline, 3-, 6-, and 9-month follow-up measurements via generalized linear mixed-effects models (GLMMs). These models will include fixed factors (intervention group, time, and the group × time interaction) and a random effect for participants to account for individual variability. The models utilize maximum likelihood estimation (MLE) methods to handle data that are missing at random (MAR). Potential confounding variables identified during the descriptive analysis were adjusted for. To account for the potential confounding effect of social interaction, perceived social support (measured via the MOS survey) will be included as a time-varying covariate in the models. The results are reported as adjusted mean differences with their respective 95% confidence intervals (95% CIs). Imputation methods will not be used.

Analysis will be performed on both an intention-to-treat (ITT) and per-protocol (PP) basis. To account for multiplicity and reduce the risk of type I error across the various secondary outcomes, *p *values will be adjusted using the Benjamini–Hochberg false discovery rate (FDR) procedure. The level of statistical significance will be set at *α* = 0.05. All statistical analyses will be conducted via STATA 17 (Stata Corporation, College Station, USA).

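### Adjustment covariates are to be picked from the trial's own between-arm descriptive comparisons, and the listed model leaves the baseline difference free, so the adjusted effect has no fixed model and gives up some precision

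*Protocol article*

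**What the plan says.** All of the analysis text is in Statistical methods of the protocol article.

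- **Descriptive step.** Continuous and categorical data are summarised, and of the continuous data it says "These data will be compared between the intervention and control groups", by t or Mann–Whitney tests. Categorical data get chi-square or Fisher tests.
- **Covariates.** "Potential confounding variables identified during the descriptive analysis were adjusted for". No candidate list, threshold or rule is given. The one covariate named in advance is social support: "perceived social support (measured via the MOS survey) will be included as a time-varying covariate in the models".
- **Model.** "Outcomes will be analyzed across the baseline, 3-, 6-, and 9-month follow-up measurements" by mixed models. "These models will include fixed factors (intervention group, time, and the group × time interaction) and a random effect for participants".
- **Reported result.** Adjusted mean differences with 95% confidence intervals. The text does not say whether these are differences in change from baseline or differences between arms at each visit.

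The section Randomization and allocation concealment stratifies on two factors, "sex (male/female) and age (above/below 71 years", and within each stratum "a block size of 2 is used to ensure an automatic 1:1 allocation ratio". Neither factor is among the listed model terms.

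**The concern.** In a randomised trial a difference between the arms in a baseline variable is chance. Imbalance is also the wrong ground for choosing a covariate, because a covariate helps through its association with the outcome. If covariates enter according to what the descriptive tables show, the adjusted effect depends on which variables were tabulated, what threshold was used and who judged it. This applies to MoCA, MMSE, nine further cognitive domains and the secondary outcomes. The Benjamini–Hochberg step corrects for the number of secondary outcomes, not for the choice of model.

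The rule also tends to pass over the covariates that the design points to. With blocks of two, the arms can differ by at most one dyad in each of the four strata (two, if each of the two assignment phases starts a fresh sequence). A test for imbalance would hardly ever flag sex or age group.

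The second part is efficiency. With baseline among the outcome times and a group main effect, the model estimates a baseline difference that randomisation says is zero in expectation. The group-by-time term is then a plain difference of changes. Precision is scarce here, and the pilot's estimates are meant to inform a larger trial.

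**Working it through.** **Inputs.** From Sample size: 51 dyads per arm, 15% attrition, MoCA difference 0.7, SD of differences 1.8. Completers per arm: 51 × 0.85 = 43.4, taken as 43. The correlation ρ between two visits is not given, so 0.5 to 0.9 is assumed.

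**The plan's own figure.** A one-sided 5% paired t calculation with 0.7 and 1.8 needs 43 for 80% power, and 43/0.85 = 50.6, hence 51 per arm and 102 in total. Repeated-measures formulas come close as well, but only with a correlation that the document does not give. The basis of that calculation is a separate matter; here it supplies only the inputs.

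**Baseline free or constrained.** A participant random intercept implies equal correlation ρ between visits. Let s be the SD at one visit and n the number per arm, with complete data.

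- Baseline free (difference of changes): variance = (2/n) × 2s²(1−ρ) = (2/n) × 1.8²
- Baseline means equal, or adjusted for baseline: variance = (2/n) × s²(1−ρ²)
- Ratio: (1−ρ²) / [2(1−ρ)] = (1+ρ)/2

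With n = 43, the free-baseline SE is 1.8 × √(2/43) = 0.388. Power is two-sided at 5% from the noncentral t. The n for 80% power is 2 × (1.960 + 0.842)² × 1.8² × ratio / 0.7².

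| Model | Variance ratio | Implied s | SE | Power, 43 per arm | n per arm for 80% |
|---|---|---|---|---|---|
| Baseline free | 1 | – | 0.388 | 43% | 104 |
| Constrained, ρ = 0.5 | 0.75 | 1.80 | 0.336 | 54% | 78 |
| Constrained, ρ = 0.7 | 0.85 | 2.32 | 0.358 | 49% | 89 |
| Constrained, ρ = 0.9 | 0.95 | 4.02 | 0.378 | 45% | 99 |

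**Leaving out the strata.** This was simulated with 43 per arm, four visits, ρ = 0.7 and strata in blocks of two, with the strata explaining 10% or 20% of the outcome variance (assumed). SEs are in units of s.

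- *Difference of changes:* 0.1671 with and without the strata, and 0.1709 either way with 15% dropout (run at 10%). Main effects that are constant over time cancel.
- *Difference at a visit, baseline free:* the reported SE is 0.2157 without strata, against 0.2046 (10%) or 0.1929 (20%) with them. The ratios are 1.05 and 1.12. The actual spread of the estimate was the same with and without strata, so omission makes the reported SE too large.
- *Constrained-baseline model:* 0.1540 without strata, against 0.1525 or 0.1506 with them. The variance falls by a further 2% or 4%.

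**Selection on imbalance.** This was simulated under no treatment effect with 43 per arm, 5 or 10 candidate covariates that jointly explain 20% or 40% of the variance, and entry at p < 0.05 or p < 0.20. Type I error at a nominal 5% was about 3% to 4.5%.

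**The case against.** The strongest reply has four parts.

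1. **The listed model is standard and valid.** Group, time and their interaction with a participant random effect gives an unbiased estimate under randomisation. This stands. A reader might infer bias from the free baseline difference, but the only cost is efficiency. The size of that cost depends on an assumed ρ and shrinks to 5% of the variance at ρ = 0.9.
2. **Not naming the strata does not exclude them.** This is a condensed article, and the full analysis plan may add them. This also stands, so their absence from the list is not a fault in itself. It matters because the one route that the text gives for further covariates would rarely admit them.
3. **The strata cost nothing for a change contrast.** Correct. It is tempting to say that leaving them out wastes precision throughout. The simulation shows no loss for a difference of changes, and an effect only for visit-wise differences or in a baseline-adjusted model. The document does not say which contrast is reported, so the point stays open but small.
4. **The stakes are limited.** Feasibility is the primary outcome and is judged on recruitment, retention and adherence, which need no covariate model. Cognition is exploratory, and the analyst works with arbitrary group codes until the primary analysis is complete. This lowers the severity. Blinding limits steering towards a favoured arm, but it does not fix the model in advance.

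The reply does not reach the selection sentence. It is a stated rule, not a detail left to another document.

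**Conclusion.** The point holds at modest severity. The protocol states a data-driven rule for choosing covariates, so its adjusted mean differences have no fixed model behind them. This does not depend on any assumed figure. It does rest on reading the descriptive analysis as the between-arm tests in the same section, which are the only ones described.

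The loss from the free baseline is real but uncertain: 5% to 25% of the variance for ρ from 0.9 to 0.5, which moves MoCA power from about 43% to between 45% and 54%. That does not bring power near 80%, so it is a free gain and not a remedy for the sample size.

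A reader might also infer that choosing covariates from the data inflates the false-positive rate. Neither the documents nor the check supports this: selection on chance imbalance left the nominal rate inaccurate, but on the conservative side.

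**What to change.** Replace the selection sentence in Statistical methods with: *All models adjust for sex, age (above/below 71 years) and the baseline value of the outcome (or constrain the baseline means to be equal); no covariate is selected from observed between-group imbalance.* With the equal-means option, keep baseline as an outcome time and drop the group main effect. With baseline as a covariate, model only the 3-, 6- and 9-month values.

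State which contrast the adjusted mean difference is (difference in change, or difference at a named visit).

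The cost is wording only. Sex, age and the baseline scores are already collected, and neither the sample size nor the visit schedule changes.

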**Methods:**

A pilot, randomized, controlled, and double-blind clinical trial will be conducted with 102 dyads consisting of an older adult with MCI and their family study partner. The participants will be randomly assigned to two groups: the intervention group (INTERCOG) and the control group. The INTERCOG group will receive a 12-week home-based intervention (twice weekly) with the support of a healthcare professional. The intervention components consist of cognitive training and stimulation, nutritional counseling, and physical exercises. Simultaneously, family members will participate in a training program on care and self-care. The control group will receive an Enhanced Standard of Care with educational messages on infection prevention. The feasibility of the study will be assessed through an analysis of recruitment, data collection, intervention acceptability, and implementation challenges; also, changes in global cognition and changes in specific cognitive domains will be measured as exploratory results. Secondary outcomes will include changes in health-related quality of life, caregiver burden, social support for family members, as well as changes in functional independence, frailty, physical capacity, family functioning, and nutritional status in patients, with follow-up at 3, 6, and 9 months. In a subsample of 40 participants, the diversity of the gut microbiota will be characterized, and the frequency of the APOE-ε4 allele will be determined.

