### Baseline and postintervention follow-up (0, 3, 6, and 9 months)

Neuropsychological assessment: a neuropsychologist will administer tests to evaluate global cognition, and the cognitive domains will be defined as the primary outcome. Together, these tests provide a detailed profile of the key cognitive areas affected by MCI.

Nursing assessment: measurements of blood pressure and pulse will be taken with an OMROM model HEM-7130 automated monitor. In addition, the following instruments will be administered: the SF-36 Health Survey [49], Patient Characterization Form (basic information, family, pathological, pharmacological, and surgical history), Family APGAR [50], Mini Nutritional Assessment (Long-MNA®) [51], Pittsburgh Sleep Quality Index (PSQI) [52], and Bristol Stool Form Scale (BSFS) [53].

Physiotherapy assessment: dominant handgrip strength will be measured with a JAMAR 6386 hydraulic analog hand dynamometer. Weight and body composition will be assessed by bioimpedance with a Body Composition Monitor and Scale OMRON HBF 514C. Height and waist and hip circumferences will be recorded via a standardized method. Additionally, Tinetti gait and balance assessment tool [54], Senior Fitness Test [55], Linda Fried Frailty Phenotype [47], and Lawton-Brody Instrumental Activities of Daily Living Scale [46] will be administered.

Family member assessment: nursing staff will apply the GCPC-UN-D© sociodemographic form for the characterization of study partner [56]. Social support will also be assessed via the Medical Outcomes Study Social Support Survey (MOS) [57], quality of life with the SF-36 [49], and caregiver burden with the Zarit Caregiver Burden Interview [58, 59] (see Supplementary Table S3 for more details).

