## Discussion

The management of cognitive decline represents a substantial challenge, particularly in Latin American countries with progressive and accelerated population aging [65]. NPMIs are promising targets for maintaining or improving global cognitive function [11, 12], physical status, and quality of life in older adults with MCI and potentially preventing progression to dementia [66]. Given that better outcomes are associated with greater adherence [67], the primary focus of this study is the evaluation of the feasibility and implementation of the NPMI INTERCOG. Despite increasing evidence, challenges persist regarding the generalization and implementation of these interventions, due to the lack of standardization in their duration, intensity, and frequency [66]. A key strength of the NPMI INTERCOG is its comprehensive scope, which addresses not only global cognition or specific cognitive domains but also critical health dimensions such as functional independence, physical frailty, quality of life, and nutritional status.

The home-based approach of this trial aligns with the growing need for scalable and inclusive healthcare solutions. Unlike traditional clinic-based programs, home-delivered care enhances ecological validity by fostering behavioral changes in the exact setting where they must be sustained. This model not only facilitates recruitment and retention but also empowers the dyad, transforming the home into a therapeutic space that supports cognitive health without the stress associated with clinical environments.

Furthermore, the inclusion of family members is fundamental for proactively mitigating future caregiver burden and increasing perceived social support. We anticipate that linking the family will also enhance adherence to multicomponent interventions. The execution of this pilot will provide critical information for future implementations or larger-scale clinical trials by estimating recruitment and adherence rates, dropout factors, and specific implementation difficulties encountered by the intervention team. Additionally, this study offers a unique opportunity to explore the links between the gut–brain axis and variables related to the gut microbiota and evaluate the presence of ApoE risk genotypes.

Although recruitment from specific geographical areas may restrict generalizability and the intervention duration and follow-up period were designed for a pilot, the results will be important for large-scale clinical trials.

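### Adjusting the outcome models for follow-up MOS social support, which the family component is meant to raise, means the reported differences no longer estimate the total (ITT) effect

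*Protocol article*

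**What the plan says.** The Statistical methods section sets one modelling approach: "Outcomes will be analyzed across the baseline, 3-, 6-, and 9-month follow-up measurements via generalized linear mixed-effects models (GLMMs", with group, time, their interaction and a random participant effect. It then adds a covariate: "perceived social support (measured via the MOS survey) will be included as a time-varying covariate in the models". The stated reason reads: "To account for the potential confounding effect of social interaction". Results are to be reported as adjusted mean differences, on both an ITT and a per-protocol basis. The article does not limit this adjustment to baseline MOS or to a sensitivity or mediation analysis, and it names no model without MOS. On missing data, it relies on maximum likelihood under missing at random and states: "Imputation methods will not be used".

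Three other places say what MOS is in this trial:

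- **Whose score, and when.** Under the family member assessment in the section on baseline and follow-up at 0, 3, 6 and 9 months: "Social support will also be assessed via the Medical Outcomes Study Social Support Survey (MOS".
- **Its status.** The abstract's Methods paragraph: "Secondary outcomes will include changes in health-related quality of life, caregiver burden, social support for family members".
- **Its expected response.** The Discussion calls the inclusion of family members "fundamental for proactively mitigating future caregiver burden and increasing perceived social support". The Background also cites evidence that multicomponent interventions raise the social support of caregivers of patients with Alzheimer's disease.

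**The concern.** A confounder of a treatment comparison is a common cause of treatment and outcome. Allocation here is random, so nothing measured afterwards can be a cause of it. On the protocol's own account the arrow runs the other way: the family training is meant to raise perceived support.

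Holding follow-up MOS fixed therefore asks how the arms would differ if support were the same in both, which is not the ITT question. Any benefit that works through better support is taken out of the group-by-time terms. Because support and the outcomes may share unmeasured causes, such as household circumstances or the partner's mood, what is left is not a clean direct effect either.

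At stake are the effect estimates that the Abstract and Discussion say will inform a larger trial, and the secondary estimates for the partner, whose support the intervention explicitly targets.

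**Working it through.** **1. Is follow-up MOS affected by treatment?** MOS is scheduled at 0, 3, 6 and 9 months, so three of its four values come after allocation. It is a declared outcome and an intended effect of the family component. These three statements are enough to make it a post-randomisation variable on the intended causal path. No arithmetic is needed for that conclusion.

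**2. Scale for the MoCA illustration.** The Sample size section gives 0.7 for MoCA with a standard deviation of differences of 1.8. A one-sided paired t calculation (alpha 5%, power 80%) with a 0.7-point difference gives 43, and 43 / (1 - 0.15) = 50.6, rounded up to the stated 51 per group. This supports reading 0.7 as MoCA points. It serves here only as a yardstick, and the sample size is not in question in this point.

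**3. Effect removed by adjustment.** With no common causes,

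effect removed = (INTERCOG effect on MOS, in SD) x (change in MoCA per SD of MOS).

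The protocol gives neither factor. Assumed: a shift of 0.2 to 0.5 SD, and a slope of 0 to 0.6 MoCA points per SD.

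| MOS shift (SD) | Slope (points per SD) | Removed (points) | Left of 0.7 | Share removed |
|---|---|---|---|---|
| any | 0 | 0 | 0.70 | 0% |
| 0.2 | 0.2 | 0.04 | 0.66 | 6% |
| 0.2 | 0.6 | 0.12 | 0.58 | 17% |
| 0.35 | 0.4 | 0.14 | 0.56 | 20% |
| 0.5 | 0.4 | 0.20 | 0.50 | 29% |
| 0.5 | 0.6 | 0.30 | 0.40 | 43% |

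**4. Check in a model of the planned form.** Simulation with 51 per arm, four visits, group x time, a random participant intercept and 15% dropout. The residual SD was 1.27, so that the SD of a change is about 1.27 x √2 = 1.80. With a shift of 0.5 SD, a slope of 0.4 and a true total effect of 0.7, the mean estimate over 120 runs was 0.71 without MOS and 0.50 with it, in line with the table.

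**5. Missing MOS.** Likelihood estimation under missing at random covers missing outcomes. In usual mixed-model software a row with a missing covariate is left out, and imputation is ruled out. If, for illustration, 10% of MOS values were missing at visits where the patient was tested, about 38 of 377 visit rows (10%) would be lost. The standard error of the 3-month contrast would rise from 0.366 (no MOS, all rows) to 0.390 (MOS, reduced rows). The protocol gives no figure for partner-only non-response.

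**6. MOS as the outcome.** Read as written, the model for MOS would carry the same visit's MOS score as a covariate and leave no treatment effect to estimate. For the partner's SF-36 and Zarit scores, the respondent and the targeted pathway are the same as for MOS, so the over-adjustment is most direct there.

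**The case against.** The best reply is that little depends on these models. Feasibility, acceptability and adherence are the primary outcome. The progression rule uses recruitment, retention, session completion and qualitative feedback, and cognition is called exploratory. This stands: the covariate can alter neither the primary outcome nor the feasibility decision. It does still alter every effect estimate that comes from the models.

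A second reply is that the aim is reasonable. The control arm gets phone messages while the intervention arm gets home visits twice a week, so social contact is a rival explanation. That worry is fair, but a partner-reported support score is a doubtful measure of the patient's contact with visiting staff. The same weakness also limits the harm: the looser the link between partner MOS and patient cognition, the less of the cognitive effect is removed, perhaps almost none.

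A third reply is that the article condenses a fuller plan. Nobody is likely to put MOS on both sides of its own model, and MOS shares its visit schedule with the patient tests, so a missed dyad visit costs no additional row. Both are fair. The first calls for an explicit exception, and the second confines the loss to visits where only the partner's score is missing.

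A reader might go further and infer that the bias must run towards no effect, or that it removes more than half of the effect once a shared unmeasured cause is allowed for. The documents support neither. The direction depends on the signs of the paths, and common-cause bias can go either way. Very large losses come from a single-visit calculation, whereas the planned model has four visits and a random participant effect that absorbs much of a stable common cause.

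**Conclusion.** The point holds, and the plan should be changed. As written, the adjusted mean differences for cognition and the secondary outcomes are not estimates of the total ITT effect, because they condition on a post-randomisation variable that the intervention is meant to change. This follows from the protocol's own statements and does not depend on any assumed number.

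The size is unknown. The range of 6% to 43% of a 0.7-point MoCA effect rests entirely on an assumed MOS shift of 0.2 to 0.5 SD, an assumed slope of 0.2 to 0.6 points per SD and no common causes. With a zero slope the loss is nil. The extra loss of visits rests on usual software handling and on an unstated rate of partner-only missing MOS.

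The affected results are exploratory and secondary. The feasibility conclusion is unaffected, so this should be fixed but does not put the trial's primary purpose at risk.

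**What to change.** - Remove follow-up MOS from the main ITT and per-protocol models. Baseline MOS may be used as a covariate.
- Keep follow-up MOS as a secondary outcome, analysed without itself as a covariate.
- Put any model that adjusts for follow-up MOS in a separately labelled exploratory mediation or supplementary analysis, and state how visits with missing MOS are handled there.
- State the lack of an attention-matched control as a limitation, in place of trying to adjust for it.

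The cost is a one-sentence change in the analysis section and a line in the limitations. No new data, visits or participants are needed. The article reports the trial as recruiting, so the change can be recorded before any unblinded analysis.
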